# Study protocol for an effectiveness-implementation hybrid trial to evaluate a health promotion intervention in parents and their 5-year-old child: Saga Stories in health talks in Swedish child healthcare

**DOI:** 10.1186/s12889-022-14549-z

**Published:** 2022-11-25

**Keywords:** Child healthcare, Health promotion, Lifestyle behaviours, Parental self-efficacy, Pre-school

## Abstract

**Background:**

Unhealthy lifestyle behaviours such as a poor diet, inadequate physical activity, and excessive screen time have been shown to be established in childhood and track into adulthood, demonstrating the need for health promotion interventions in the pre-school years. The overall aim of this project is to: (i) evaluate the effectiveness of `Saga Stories in health talks´ within child healthcare (CHC) on parental self-efficacy to promote healthy diet, physical activity, and screen time behaviours in their child; children’s intake of key dietary indicators and screen time and (ii) evaluate and explore the implementation of `Saga Stories in health talks´ with regards to acceptability, appropriateness, feasibility, fidelity, adoption, sustainability, satisfaction, and usage.

**Methods:**

A hybrid type I effectiveness-implementation trial will be conducted. A cluster randomized controlled trial will be used to assess the effectiveness of `Saga Stories in health talks´ in 42 CHC centers across six regions in Sweden. `Saga Stories in health talks´ consists of material for CHC nurses to use to facilitate the health talk with both the child and parent(s) and is complemented with take-home material. Parent and child dyads are recruited (*n* = 450) from participating CHC centers when they attend their 5-year routine visit. The intervention group receives the health talk using Saga Stories and take-home material, whereas the control group receives the standard health talk. The primary outcome is parental self-efficacy to promote healthy diet, physical activity, and screen time behaviours in their child and secondary outcomes include children’s intake of key dietary indicators and screen time. All outcomes are assessed at baseline and 2-months post-intervention. The implementation outcomes that will be assessed are: acceptability, appropriateness, feasibility, satisfaction, usage, fidelity, adoption, and sustainability (assessed quantitatively and qualitatively).

**Discussion:**

The Swedish National Board of Health and Welfare have identified the need of more material, education, and working methods for promoting healthy lifestyle behaviours in CHC. Following this trial `Saga Stories in health talks´ has great potential to be implemented in CHC across Sweden to aid nurses to promote and support healthy lifestyle behaviours in pre-school children and their families.

**Trial registration:**

ClinicalTrials.gov, NCT05237362. Registered 2 February 2022.

## Background

Unhealthy lifestyle behaviours (e.g., a poor diet, inadequate physical activity, and excessive screen time) have been shown to be established in childhood and track into adulthood [1, 2]. According to the 2021 Generation Pep report, including a representative sample of Swedish children and youth aged 4-17 years, only 10 and 20% of children and youth met the dietary recommendations for fruit and vegetables and fish intake as well as physical activity, respectively. Furthermore, 54% of parents of 4-6 year olds reported 1-2 hours of screen time the previous day and another 14% reported 3-4 hours of screen time [3]. Parental self-efficacy has been found to be associated with children’s dietary, physical activity, and screen time behaviours [4, 5], thus there is a need for health promotion interventions in the pre-school years to aid parents in encouraging healthy behaviours and minimizing unhealthy ones.

Child healthcare (CHC) in Sweden reaches 99% of all children [6] and CHC nurses meet parents and children continuously from birth until 5 years of age at regular check-ups [7]. Thus, this makes CHC an ideal arena for health promotion interventions aimed at promoting healthy lifestyle behaviours in families with young children. Furthermore, the Swedish National Board of Health and Welfare have identified the need for more material, education, and working methods for promoting healthy lifestyle behaviours within CHC [6]. This was further emphasized in a recent study where the majority of Swedish CHC nurses reported not feeling comfortable discussing screen time with parents. They stated that they felt that this is a new topic and do not have enough material to support their discussions [8].

Within CHC in Sweden, health talks and guidance on promoting healthy lifestyle behaviours are part of routine visits from 3 months of age [7]. However, previous research has indicated that lifestyle behaviours such as dietary habits, physical activity, sleep, and screen time are infrequently discussed at routine visits in CHC [9]. As health talks vary depending on the needs of the family, a variety of scientifically evaluated material needs to be available to CHC nurses in order for them to be able to comfortably and effectively have a dialogue with parents and their child regarding lifestyle behaviours.

## Aims

The aim of this protocol is to describe the study design and methodology of `Saga Stories in health talks´. The main objectives are:(i)to evaluate the effectiveness of `Saga Stories in health talks´ on (a) parental self-efficacy to promote healthy diet, physical activity, and screen time behaviours in their child (primary outcome); (b) children’s intake of fruit and vegetables as well as sweet beverages (secondary outcomes); and (c) children’s screen time (secondary outcome).(ii)to evaluate and explore the implementation of `Saga Stories in health talks´ with regards to acceptability, appropriateness, feasibility, fidelity, adoption, sustainability, satisfaction, and usage.

## Methods

This project will use a hybrid type I effectiveness-implementation trial design, as our primary focus is effectiveness and our secondary focus is implementation [10]. A mixed-methods approach will be used to collect data and the `Outcomes for Implementation Research´ [11] evaluation framework was used to inform the evaluation plan. The study design is shown in Fig. 1.

**Fig. 1 Fig1:**
[figure not shown]
Flow chart of the `Saga Stories in health talks´ study design

### Effectiveness evaluation

#### Study design, recruitment, and participants

`Saga Stories in health talks´ is a cluster randomized controlled trial which will be conducted in six regions throughout Sweden (Dalarna, Norrbotten, Värmland, Västernorrland, Västra Götaland, and Örebro). The intervention group receives the health talk using Saga Stories and take-home material, whereas the control group receives the standard health talk. Eligible families are provided with oral and written information regarding the study from their CHC nurse at the routine five-year check-up. If the accompanying parent consents to participate they will scan a QR code to sign the informed consent using BankID (a secure digital signature) and directly after they will fill in the baseline questionnaire. To be included in this study, the accompanying parent needs to be able to understand and read Swedish sufficiently well in order to provide informed consent and partake in the Saga Stories health talk. There are no exclusion criteria. This study is reported according to the SPIRIT 2013 statement [12] and Table 1 shows a trial participant timeline.

**Table 1 Tab1:** Participant timeline according to SPIRIT

	STUDY PERIOD			
	Enrollment	Allocation	Post-allocation	Close-out
Time point	0	0	2 months	2 months
	5-year routine visit			

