#### Randomization and blinding

Forty-two CHC centers with 1-7 nurses per center were randomly assigned to the two treatment groups (22 CHC centers in the intervention and 20 in the control group). To ensure balance, we stratified the randomization by geographical regions and center size. Two CHC centers dropped-out before the trial was initiated due to high absenteeism because of the COVID-19 pandemic. Therefore, there is 22 CHC centers in the intervention group and 18 in the control group. Due to the nature of the trial, CHC nurses and participants cannot be blinded; however, outcome assessors are blinded to the treatment allocation of the participating families.

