### Implementation evaluation

#### Study design

The implementation evaluation is taking place in the 22 CHC centers allocated to the intervention arm. All participating nurses were informed (orally and in text) about the evaluation and provided informed consent before participating. Prior to the implementation of `Saga Stories in health talks´, all participating CHC nurses attended a half-day online education on how to use the Saga Stories material in their health talks, as well as how to recruit parents to the study. During the entire intervention period the nurses have access to an online folder with study information, commonly asked questions, as well as the `Saga Stories in health talks´ materials for printing when needed. The nurses also have the possibility to contact the research team by phone or email if they have other questions pertaining to the study or intervention material. Once a month, the nurses receive a newsletter with information on the status of recruitment and reminders on how to use the Saga Stories materials. In addition, two or three times per year, all nurses in the intervention group are invited to participate in an online discussion forum for 1 h, to share experiences with each other. These forums are voluntary and focus on different topics such as talking about challenging or sensitive topics e.g., children’s growth chart and BMI.

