##### Fidelity and adoption

A checklist will be used to assess implementation fidelity. Following every five-year check-up, each CHC nurse will use the checklist to indicate whether they have followed the implementation procedures. Within the checklist there is room to provide open ended notes. The checklist includes the following questions: 1. Did you use the ‘Saga Stories’ material (Yes or No); 2. If you did not use the material, why not? (Lack of time, Used other material instead, The family did not want the health talk, Prioritised something else during the visit, Other - please specify); 3. Which parts of the flipchart did you use during the health talk (Food, Physical activity and sedentary behaviour, Sleep, Dental health, and Bathroom habits); 4. Did you send the take home material with the family? (Saga Stories book, Fruit and vegetable bingo, Physical activity fortune teller, Ideal 24-hour period, None of them). Adoption is assessed through the CHC nurses’ documentation within the checklist. Here they will be asked to record when they have had a five-year check-up and whether or not they have used the Saga Stories material to facilitate the health talk. Fidelity and adoption will be assessed throughout the implementation period.

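### Unblinded nurses recruit after centres are allocated, under a criterion partly worded around the intervention talk, and the adjusted model would not correct resulting differences between families

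*Protocol article*

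**What the plan says.** Four parts of the protocol article bear on this point.

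- **Order and blinding** (Randomization and blinding): "Forty-two CHC centers with 1-7 nurses per center were randomly assigned to the two treatment groups". Then: "Two CHC centers dropped-out before the trial was initiated due to high absenteeism because of the COVID-19 pandemic". The counts go from 22 and 20 to 22 and 18, so allocation was fixed before the first family was seen. On blinding: "CHC nurses and participants cannot be blinded". Only outcome assessors are blinded.
- **Recruiter and criterion** (Study design, recruitment, and participants): "Eligible families are provided with oral and written information regarding the study from their CHC nurse at the routine five-year check-up". The accompanying parent must understand and read Swedish "sufficiently well in order to provide informed consent and partake in the Saga Stories health talk". The section adds: "There are no exclusion criteria".
- **Reason for the criterion and biases acknowledged** (Discussion): the language restriction is explained as a way to secure delivery of the intervention. The bias attributed to lack of blinding is social desirability.
- **Analysis** (Statistical analyses): linear random-effects models with centre as a random effect, unadjusted and adjusted for child age and sex. Parental education appears only among the planned interaction analyses.

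**The concern.** Cluster randomisation makes the centres comparable in expectation. It does not do the same for families enrolled afterwards by staff who know the arm. A nurse who has the flipchart and book in hand may read the criterion as a question about who would manage that talk. A control nurse has to apply the same words to a talk that will not take place. The families presented with the study, or judged to meet the criterion, could then differ between arms in language skill, education, motivation or starting self-efficacy.

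The primary outcome is self-reported parental self-efficacy, which plausibly depends on those characteristics. A difference at entry would shift the estimated effect, and recruiting more families would not remove the shift. Child age and sex are unlikely to carry such differences, so the stated adjustment offers little protection.

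**Working it through.** **Is the mechanism in the text?**

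1. Allocation came before recruitment: centres were already assigned, and two left before the trial began.
2. The recruiter knows the arm: the family's own nurse presents the study, and nurses are not blinded. Blinded outcome assessment does not affect who is enrolled.
3. The criterion has two parts. Reading Swedish well enough to consent is arm-neutral. Being able to take part in the Saga Stories talk describes something that happens in one arm only.
4. Stratification by region and centre size balances centres, not the families chosen within them.

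Table 1 lists cluster allocation at time 0, after screening and consent. The Randomization and blinding section gives the actual order, and the two should be reconciled.

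**What could baseline data show?** Baseline self-efficacy, diet and screen time, and the parent's age, sex and socioeconomic position, are collected with no restriction to one arm. The planned interaction analyses imply that education is recorded too. A comparison by arm would show imbalance in these. It would not show how many families were seen, invited or declined, nor unmeasured motivation.

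**How far would a shift matter?** The document gives no figure for this, so what follows is illustration only.

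Inputs: a four-point target and 80% power (Sample size section); two-sided 5% level (assumed, not stated).

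- Implied standard error of the arm difference = 4 / (1.960 + 0.842) = 1.43 points.
- With no true effect and an enrolment shift of b points, false-positive rate = Φ(b/1.43 − 1.96) + Φ(−b/1.43 − 1.96).

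| Assumed shift b | False-positive rate |
|---|---|
| 0.5 | 6.4% |
| 1 | 10.8% |
| 2 | 28.8% |

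**Why adjust for baseline?** Let d be a baseline difference produced by enrolment (intervention minus control) and ρ the baseline–follow-up correlation. Assume equal SDs at both times, no true effect, and a common slope ρ between and within arms. The bias is ρd for a follow-up-only comparison, (ρ − 1)d for change, and ρd − ρd = 0 once baseline is in the model. For d = 1 point:

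| ρ (assumed) | Follow-up only | Change | Baseline-adjusted |
|---|---|---|---|
| 0.4 | +0.4 | −0.6 | 0 |
| 0.6 | +0.6 | −0.4 | 0 |
| 0.8 | +0.8 | −0.2 | 0 |

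The first two columns have opposite signs. If intervention centres enrolled parents with higher starting self-efficacy, a follow-up-only comparison would favour the intervention and a change analysis would count against it. Adjustment removes only the part carried by measured baseline values.

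**The case against.** The case on the other side is substantial, and it limits how far the point goes.

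- A reader might infer that nothing collected in the control arm could reveal selection. That is not so: baseline outcomes and parental characteristics are collected in both arms. Only invitation and uptake are undescribed.
- A reader might infer that the criterion is meaningless in control centres, or that each nurse freely chooses whom to invite. The document supports neither. The consent-reading part applies equally in both arms, the rule is stated once for both, and the text does not say who judges it. It says that eligible families are informed, and there are no exclusion criteria.
- A reader might infer that only intervention nurses were prepared for recruitment, because training on the intervention material "as well as how to recruit parents to the study" and the newsletter on recruitment status are described for them alone. Both appear in the implementation evaluation, which is confined to the 22 intervention centres and would not describe control procedures. A condensed article may leave those out. Likewise, the form in Fidelity and adoption ("Following every five-year check-up, each CHC nurse will use the checklist") measures use of the material. Its listed questions do not cover invitation or consent, so it is not a recruitment log in either arm.
- The baseline questionnaire already follows directly after consent, at the start of the visit. That protects baseline answers from exposure to the talk itself.
- Covariate choice is often refined in an analysis plan that is not shown here. However, the article does state an adjusted model, and that stated set is what is assessed.

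What stands is the order of events, the unblinded recruiter, the arm-specific half of the criterion, the absence of this bias from the limitations, and the narrow covariate set.

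**Conclusion.** The concern holds as a risk the design leaves open. Nothing in the document shows that the arms have enrolled different families, and no size can be derived from it. The 6%, 11% and 29% rest on assumed shifts of 0.5, 1 and 2 points and an assumed two-sided 5% level. They show sensitivity and are not an estimate. It would also be wrong to quote one percentage of the four-point target as the bias, since its direction depends on whether follow-up scores or changes are compared. The point merits action because the most useful remedy, a better adjusted model, uses data already collected. That remedy reduces bias from measured differences; it cannot correct differences in who was invited or in unmeasured motivation.

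**What to change.** 1. **Adjusted model.** For the primary and secondary outcomes, add the baseline value of the outcome and parental education to child age and sex, and report baseline characteristics by arm. No new data are needed, and baseline adjustment should also improve precision. Fix this before outcome data are examined by arm.
2. **Criterion.** Make the wording arm-neutral, for example: the parent understands and reads Swedish well enough to consent and to complete the visit without an interpreter.
3. **Uptake.** Where feasible for the remaining recruitment, keep a simple count in both arms of five-year visits held, families invited and families consented. Report uptake by arm, and name recruitment bias as a limitation beside social desirability.

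Cost: slight extra paperwork for nurses. Recruitment began in February 2022, so items 2 and 3 create a before/after difference in eligibility wording and logging. Record the date of change and report it. Item 1 has no such drawback.

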**Enrollment**				
Eligibility screen	X			
Informed consent	X			
Allocation (cluster)		X		
**Interventions**				
Intervention		X		
Control		X		
**Assessments**				
Baseline questionnaire	X			
Child height/weight	X			
Self-efficacy questionnaire	X		X	X
Intervention evaluation			X	X

#### Randomization and blinding

Forty-two CHC centers with 1-7 nurses per center were randomly assigned to the two treatment groups (22 CHC centers in the intervention and 20 in the control group). To ensure balance, we stratified the randomization by geographical regions and center size. Two CHC centers dropped-out before the trial was initiated due to high absenteeism because of the COVID-19 pandemic. Therefore, there is 22 CHC centers in the intervention group and 18 in the control group. Due to the nature of the trial, CHC nurses and participants cannot be blinded; however, outcome assessors are blinded to the treatment allocation of the participating families.

#### Intervention

At the 5-year routine visit at primary (CHC), health talks where nurses provide information about healthy lifestyle behaviours (e.g., diet, physical activity, screen time etc.) are mandatory in all regions in Sweden. `Saga Stories in health talks´ consists of material for CHC nurses to use as a tool to facilitate the health talk with both the child and parent(s) and is complemented with take-home material for the families. Every nurse will receive a large flipchart with colourful pictures and text to facilitate their health talk at the five-year check-up. The flipchart includes information and suggested questions regarding food, physical activity and sedentary behaviour, sleep, dental health, and bathroom habits. Depending on the needs of the family the nurse can focus on the subjects most applicable to that family and tailor the health talk using the ‘Saga Stories’ material. For instance, if a family feels they are struggling with food and do not perceive physical activity and sedentary behaviour as a problem the majority of the health talk may be focused upon food. Thus, some health talks will include all subjects while others may only focus on one or two subjects. At the conclusion of the check-up the children receive the book `Saga Stories: Your amazing body and brain´, which is an inspirational and educational book which the parents are encouraged to read together with their child. The parents are given a hand-out showing an ideal 24-hour period with regards to time spent sleeping, playing, being physically active, and using screens for five-year olds. They also receive games for the child to take home (fruit and vegetable bingo and a physical activity fortune teller), which are intended to promote healthy lifestyle behaviours. The intention of the games and book is to create curiosity and interest in the child (together with their parents) for new foods and active play. Figure 2 shows pictures of the intervention material and Table 2 provides a more detailed description of the intervention material.

**Fig. 2 Fig2:**
[figure not shown]
Screen shots of the Saga Stories material illustrated by [name]. The top row shows example pages of the Saga Stories flip chart used by the child healthcare nurses to facilitate the health talk at the five-year routine visit. These include a) the front page illustrating the four topics (food, physical activity and sedentary behaviour, sleep, dental health, and bathroom habits); b) an example from the healthy food habits pages, and c) an example of the physical activity and sedentary behaviour pages in the flip chart. The bottom row shows the take-home material that is given to the families at the visit: d) the Saga Stories book, e) the physical activity fortune teller, and f) the fruit and vegetable bingo

**Table 2 Tab2:** Detailed description of the Saga Stories in health talks material

Material included in Saga Stories in health talks	Purpose of the material	What the material consists of	Target behaviour in relation to the study
Flipchart for child healthcare nurse	A flipchart to help the nurse facilitate the health talk at the 5-year routine visit at primary child healthcare.	The flipchart consists of colourful pictures and text covering the following topics: food; physical activity and sedentary behaviour; sleep; dental health; and bathroom habits.	- Parental self-efficacy to promote healthy diet, physical activity, and screen time behaviours - Children’s intake of fruit, vegetables, and sweet drinks - Children’s screen time
Saga Stories: Your amazing body and brain	An inspirational and educational book covering the topics covered in the health talk that parents are encouraged to read together with their child at home.	A book featuring a story about the characters Saga and Samir building an obstacle course together. The book includes easy facts about the body and what happens when we move, but also includes a part with information directed only to parents.	- Parental self-efficacy to promote healthy diet, physical activity, and screen time behaviours - Children’s intake of fruit, vegetables, and sweet drinks - Children’s screen time
The “Pep” 24-hour day poster	To give the parents an overview of what a typical 24-hour period should look like for a 5-year-old child with regards to sleep and rest, play and development, movement and physical activity, and screen time.	Hand-out (A4 size)	- Parental self-efficacy to promote healthy diet, physical activity, and screen time behaviours - Children’s screen time
Fruit and vegetable bingo	To promote healthy dietary behaviours through a game by encouraging children to try a wide variety of fruits and vegetables without pressure. This material is targeted to the parents and the child.	Hand-out (A4 size)	- Parental self-efficacy to promote healthy diet, physical activity, and screen time behaviours - Children’s intake of fruit, vegetables, and sweet drinks
Physical activity fortune teller	To promote physical activity and reduce sedentary time through play. This material is targeted to the parents and the child.	Hand-out (the child and the parent fold it into a fortune teller)	- Parental self-efficacy to promote healthy diet, physical activity, and screen time behaviours

`Saga Stories in health talks´ was created by Generation Pep (a non-profit organization working with health promotion in Swedish children and youth [13]) together with the publisher Bonnier Carlsen, and author [name]. This material was also developed in collaboration with CHC nurses, dieticians, pediatricians, and researchers in an iterative process. In 2021, the `Saga Stories in health talks´ material was pilot tested in 11 CHC centers in three regions in Sweden (Halland, Sörmland, and Östergötland). Semi-structured interviews were conducted with a sample of participating CHC nurses (*n* = 17) and parents (*n* = 11) who received the health talk using the Saga Stories material. The information that was obtained from the qualitative pilot studies was used to adapt the Saga Stories material and inform the study design. The results from the pilot work will be reported elsewhere.

